## Abstract

**Background:**

Cardiovascular diseases (CVDs) increasingly contribute to morbidity and mortality in Tanzania. Public knowledge about CVD risk factors is important for the primary prevention of CVDs and can be improved through community-based interventions delivered by community health workers (CHWs). However, evidence of the utility of CHWs in improving knowledge and CVD risk factors profile is lacking in Tanzania. This study aims at assessing the effect of training CHWs and their CVD-specific interventions for reduction of hypertension and other CVD risk factors among adults in Morogoro, Tanzania.

**Methods:**

This study will use a mixed-methods design with both quantitative and qualitative approaches. A baseline quantitative survey will be conducted to assess knowledge, prevalence, and determinants of CVD risk factors in a random sample of 2950 adults aged 25–64 years. A cluster randomized controlled design with pre-test will be used to assess the effects of CVD-specific interventions delivered by CHWs on reduction of blood pressure and proportion of other CVD risk factors among 516 adults with raised blood pressure from 12 randomly selected villages in Morogoro, Tanzania. Focus group discussion (FGDs) will be conducted at the end of the intervention to assess perceived quality and acceptability of CVD-specific interventions delivered by CHWs.

The intervention will consist of a five-day CVD-specific training to CHWs from villages randomized to the intervention. Trained CHWs will then provide home health education and healthy lifestyle promotion for prevention of CVD risk factors, counseling about hypertension screening for early identification, and referral and linkage of individuals with elevated blood pressure to health facilities. Since intensity of the intervention is key to reinforce behavior change, CHWs will visit the participants every month for the first six months, then bi-monthly thereafter up to 12 months. Except for referral of participants with raised blood pressure identified during the baseline survey, control villages will not receive any interventions delivered by CHWs. At the end of the intervention period, an end-line survey will be conducted in both intervention and control villages to evaluate changes in knowledge, blood pressure, and proportion of other CVD risk factors.

**Discussion:**

The results of this study are likely to have positive policy implications for the prevention of CVD risk factors through the use of CHWs in the provision of CVD-specific interventions, especially now that the Tanzanian government is considering implementing and scaling up a nation-wide multitask CHW cadre.

**Trial registration:**

PACTR Registry, PACTR201801002959401. Registered on 10 January 2018.

**Electronic supplementary material:**

The online version of this article (10.1186/s13063-018-2924-9) contains supplementary material, which is available to authorized users.

## Background

In 2015, cardiovascular diseases (CVDs) accounted for an estimated 17.7 million deaths (nearly one-third of all global deaths), with more than two-thirds of CVD-related deaths occurring in low- and middle-income countries (LMICs) [1]. CVDs are projected to be the leading cause of death and disability globally, accounting for more than 24 million deaths by 2030 [2]. The increasing burden of CVDs in LMICs is fueled mainly by four modifiable risk factors, namely smoking, excessive alcohol drinking, sedentary life style accompanied by physical inactivity, and unhealthy dietary habits characterized by consumption of high energy-dense foods [3]. Tanzania is not spared by the increasing burden of CVDs as available data indicate rising trends of CVD risk factors [4, 5]. In the 1990s, prevalence of hypertension and diabetes in Tanzania was < 0.5%, while that of overweight and hypercholesterolemia was 5.4% and 7%, respectively [6, 7]. In recent years, CVD risk factors have increase dramatically, especially among young and middle-aged adults [4], contributing to significant morbidity, disability, and mortality [8–10]. Prevalence of hypertension has been reported to be as high as 57% with that of severe hypertension at 30%. Obesity, diabetes, and metabolic syndrome are 23%, 6%, and 38%, respectively [5]. The annual incidence rate of stroke has been reported to be 94.5 per 100,000 people in rural settings and 107.9 per 100,000 people in urban settings [9].

CVD-related mortality has declined significantly in high-income countries (HICs), largely because of effective interventions that focused on reduction of population risk factors such as high blood pressure, smoking, and hypercholesterolemia [11–13]. In Finland, such interventions accounted for 53–72% of the decline in coronary heart disease (CHD) mortality between 1982 and 1997, while improved treatments explained only 23% [11]. In England and Wales, the reduction of population risk factors accounted for 58% of the decline in CVD mortality between 1981 and 2000 [14]. Similarly, the decline in CHD mortality in the Netherlands between 1997 and 2007 was attributable to decreases in risk factors and treatment of heart failure and chronic angina in the community [13]. On the other hand, CVD-related mortality continues to rise in most LMICs causing premature and preventable loss of life [15]. Despite the rising burden, there is a lack of appropriate responsive interventions for the primary prevention of known risk factors. Additionally, the health systems in most LMICs are weak and unprepared to deal with the double burden of both prevalent infectious diseases and that of rising non-communicable diseases (NCDs). Thus, population-wide measures that are cost-effective, sustainable, and scalable are best buys for the prevention and control of CVDs in LMICs [16].

Community-based interventions implemented by community health workers (CHWs) have already shown promising benefits in reducing hypertension, incidence of diabetes, improved body weight, and changes in behavior related to physical activity, dietary habits, and smoking [17–20]. However, little evidence is available on their utility towards prevention of CVD risk factors in African settings with varying sociocultural and economic developments [21, 22].

In Tanzania, CHWs are defined as members of the community who are chosen by, and accountable to, the community to provide preventive and health promotion services to their community [23]. They act as the link to bridge cultural and language barriers, expanding access and coverage of health services and thus improving the health outcomes of their community. CHWs have been involved in implementing the interventions for maternal, newborn, child, and adolescent health services [24]. This proposed intervention study is timely in Tanzania as the government plans to roll out multi-task CHWs who will be integrated into the health system for sustainability country-wide [25]. This provides an opportunity to use CHWs to address CVD risk factors at a community level and to implement appropriate interventions for primary prevention.

The study will apply the health belief model (HBM), the first theory that exclusively focused on health-related education and health promotion [26]. The HBM has six constructs of perceived susceptibility, perceived severity, perceived benefits of taking a preventive action, perceived barriers, cues to action, and self-efficacy. HBM has been applied to interventions focusing on hypertension in different settings and populations with success [27, 28]. The findings of this study will provide evidence on the effect of the CHWs’ home-delivered intervention for reducing hypertension and other CVD risk factors and will inform the national initiatives for the prevention of CVD risk factors in Tanzania.

## Methods

### Trial design

This study will use a mixed-methods design with both quantitative and qualitative approaches. A baseline quantitative survey will be conducted to assess knowledge, prevalence, and determinants of CVD risk factors in a randomly selected sample of adults aged 25–64 years. Pre- and post-test design will be used to assess changes in knowledge of the CHWs about CVD risk factors following a five-day CVD-specific training. Trained CHWs will then provide home health education and healthy lifestyle promotion for the prevention of CVD risk factors in the selected intervention villages in Morogoro. A cluster randomized controlled design with pre- and post-intervention design will be used to assess the effects of interventions delivered by CHWs on the knowledge and proportion of CVD risk factors. Qualitative techniques will be used to conduct focus group discussion (FGDs) to participants with elevated blood pressure identified during baseline survey to assess their perceptions about quality and acceptability of the CHWs to deliver CVD-specific interventions. FGDs will be conducted at the end of intervention period.

### Trial site

The study will be conducted in the Kilombero and Ulanga districts within the Morogoro region, approximately 450 km south-west of Tanzania’s commercial capital of Dar es Salaam. The two districts have a population of 407,880 and 265,203, respectively [29]. Kilombero and Ulanga have comparable sociodemographic and economic characteristics, with rice farming being the main economic activity.

The Kilombero and Ulanga districts are selected for this intervention study because of the high number of trained CHWs recorded (14 per 10,000 population) [30] and the reports of rising deaths from NCDs [8]. Data from the Ifakara health and demographic surveillance systems (HDSS), which covers an area of 2400 km^2^ across Kilombero and Ulanga districts, indicated an 8% (16–24%) increase in the number of deaths from NCDs over a period of four years in 2003–2007, with CVDs being the most common NCD-related cause of death [8].

### Participants and eligibility criteria

This study will comprise two groups of participants: CHWs and community members.Community health workers

CHWs from villages selected for the intervention will participate in the training and delivery of the intervention in their villages. They will be assessed on their level of knowledge about CVD risk factors before and after the training session as well as at the end of the intervention to assess knowledge decay. Selected CHWs will have a minimum of four years of secondary education and will have received training for becoming a CHW.2.Community members

Participants for the baseline survey will include adults aged 25–64 years who are residents of the study villages and who will provide a written informed consent. A resident will be defined based on the HDSS definition as an individual who has stayed in a household within the study village for at least four months continuously, regardless of whether s/he has slept in that household a night before the interview [31]. A household will be defined as group of people who are served from the same pot. Exclusion criteria for cross-sectional surveys will include age outside the specified range, non-residents of the study villages, bed-ridden and/or mentally ill members, and the inability or refusal to provide informed consent for participation.

Participants with elevated blood pressure will be eligible and invited to participate in the CHWs’ home-delivered intervention focusing on health education and healthy lifestyle promotion for the prevention of CVD risk factors. An end-line survey will be conducted to all participants in the intervention study. At the end of the intervention period, a sub-group of participants from villages randomized to the intervention will be randomly selected and invited to participate in FGDs, to assess their perceptions on quality and acceptability of the CHWs’ delivered interventions for the prevention of CVD risk factors.

### The intervention

The intervention package will comprise the following: (1) training of CHWs on CVD factors; (2) home health education and healthy lifestyle promotion; and (3) referral and linkage to health facilities. The intervention will be implemented monthly for the first six months, then bi-monthly up to 12 months. Details of the intervention components are described below.Training of CHWs on CVD risk factors

The first component of the intervention is to provide a five-day training to CHWs from the intervention villages on CVD risk factors. The training will be designed and conducted based on the WHO training manual for the prevention of NCDs and healthy lifestyle [32] and the Tanzanian Curriculum for Basic Technician Certificate in Community Health (a curriculum used for the one-year CHW training course) [33]. For the purpose of this training, only CVD-related topics within the Tanzanian curriculum will be covered. The training will include slow-paced lectures, in-class exercises, and practical sessions. Briefly, the training will cover the following:i.*Definition and overview of major CVDs.* A brief overview of the major CVDs common in Tanzania such as cerebrovascular diseases, coronary heart diseases, hypertensive heart diseases, and heart failure. Will be covered during the training.ii.*Overview of both modifiable and non-modifiable CVD risk factors.* Modifiable behavioral CVD risk factors to be covered will include smoking, excessive alcohol drinking, sedentary lifestyle, unhealthy dietary habits, psychosocial stress, and socioeconomic status. Non-modifiable risk factors will include age, gender, genetic/family history, and ethnicity/race.iii.*Obtaining and calculating body measurements.* CHWs will be trained how to measure body weight, height, waist and hip circumferences as well as how to calculate and interpret body mass index (BMI) and waist-to-hip ratio (WHR). They will also receive training on how to measure and interpret blood pressure using an automated upper arm Omron blood pressure monitor and fasting blood glucose using a point-of-care device.iv.*Screening procedures and interpretation of results.* CHWs will be trained on the concept of screening for CVD risk factors with an emphasis on overweight and obesity (classification and BMI cut-offs for overweight and obesity), hypertension (blood pressure measurement and cut-offs for hypertension), and diabetes mellitus (DM) (fasting blood glucose measurements and cut-offs for DM).v.*Home health education and healthy lifestyle promotion.* CHWs will be trained on the importance of smoking cessation, reduction of excessive alcohol drinking, healthy dietary habits (such as high consumption of green leafy vegetables and fresh fruits, low salt diet, use of vegetable cooking oil, and use of whole grains), physical activity and exercise as well as regular health check-ups.vi.*Effective communication for behavior change.* Behavior change is central to the success of this intervention. An experienced behavioral change communication specialist from Muhimbili University of Health and Allied Sciences will train CHWs on effective behavior change communication strategies and skills for healthy lifestyle behavior change.2.Home health education and healthy lifestyle promotion

Following the training, CHWs in the intervention villages will provide health education to raise awareness about CVD risk factors and promote healthy lifestyles during home visits. The health messages will focus on information pertaining to the deleterious effects of CVD risk factors, maintaining normal/ideal body weight, smoking cessation, reduction of excessive alcohol drinking, reduction of salt intake, increased consumption of fruits and green leafy vegetables, use of vegetable cooking oil, and use of unrefined cereals. CHWs will also review and provide flyers/brochures on CVD risk factors to participants for their reference. CHWs will use motivational and effective communication for behavior change to encourage participants to change unhealthy lifestyle behaviors.3.Referral and linkage to health facility

In both the intervention and control villages, participants found to have elevated blood pressure and elevated fasting blood glucose during the baseline survey will be given referral notes to the health facility for further evaluation and appropriate management using standard Tanzanian guidelines. For intervention villages, CHWs will conduct routine follow-ups and ask about their attendance to health the facility as they were advised. For those who will have not attended, reasons for non-attendance will be inquired. The intervention package is summarized in Table 1 below.

**Table 1 Tab1:** Summary of activities and assessments for intervention and control villages

Activity	Interventions and assessments	
	Intervention villages	Control villages
1. Baseline cross-sectional survey a. Sociodemographic characteristics b. Knowledge of CVD risk factors c. Proportion of CVD risk factors	Yes	Yes
2. Pre-training assessment of CHWs on knowledge about CVD risk factors	Yes	–
3. Training of CHWs on interventions for CVD prevention	Yes	–
4. Post-training assessment of CHWs on knowledge about CVD risk factors	Yes	–
5. Monthly CHW home-delivered interventions (M1–M6) a. Home health education b. Healthy lifestyle promotion c. Measurements (BP and anthropometrics)	Yes	–
6. Bi-monthly CHW home-delivered interventions (M7–M12) a. Home health education b. Healthy lifestyle promotion c. Measurements (BP and anthropometrics)	Yes	–
7. Focus group discussions for perceived quality and acceptability of CHWs to deliver CVD-specific interventions	Yes	–
8. Post-intervention assessment of CHWs for knowledge decay	Yes	–
9. End-line cross-sectional survey a. Sociodemographic characteristics b. Knowledge of CVD risk factors c. Proportion of CVD risk factors	Yes	Yes

### Outcome measures

#### Primary outcome

The primary outcome measure is change in mean systolic blood pressure at 12 months in the intervention villages compared to control villages. The study aims to detect a mean change of ≥ 6.5 mmHg in systolic blood pressure (SBP) in the intervention villages compared to control villages.

#### Secondary outcomes

Secondary outcome measures will include: (1) change in mean diastolic blood pressure at 12 months; (2) change from baseline in the proportion of overweight/obesity, smoking, alcohol intake, unhealthy dietary habits, and physical inactivity; (3) change from baseline in the proportion of individuals at high risk for CVD (10-year risk for CVD > 30%); (4) perceptions about quality and acceptability of CVD-specific interventions delivered by CHWs; and (5) CVD knowledge decay among CHWs at 12 months after training.

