### Sample size estimation

This will be a two-arm cluster randomized controlled trial using villages as units of randomization. The minimum sample size for the baseline cross-sectional survey is estimated according to the methods proposed in the WHO STEPwise approach to chronic disease risk factors surveillance (STEPS) [34]. The sample size is calculated for 95% confidence intervals (CI) (z = 1.96) on the basis of a 5% margin of error and an estimated prior population prevalence of hypertension of 25.9% from the nation-wide representative STEPS survey in Tanzania [35], a design effect of 1 and an anticipated attrition rate of 20%. Participants will be adults aged 25–64 years and categorized into four age groups for each sex, resulting in eight strata. The resulting sample size is 2950. Participants with elevated blood pressure during the baseline survey will be eligible and invited to participate in the intervention study.

The sample size for the intervention study is calculated to provide an 80% power to detect a ≥ 6.5 mmHg difference in mean SBP between the intervention and control villages at an alpha level of 5%, assuming an attrition rate of 20%, an inter-cluster correlation of 0.03, and a standard deviation (SD) of SBP of 15 mmHg. The resulting sample size is 258 participants per arm of six villages. Thus, the total sample size for intervention study will be 516 participants from 12 villages.

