#### End-line survey

An end-line evaluation survey for participants in the intervention study will be conducted by an independent team. Outcome variables of interest assessed during baseline will be re-assessed during end-line to allow for assessment of changes in blood pressure, knowledge, and proportion of CVD risk factors following the CHWs delivered interventions.

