##### Anthropometrics

Anthropometric measurements will include weight, height, and waist circumference taken using standard procedures. Briefly, all anthropometric measurements will be taken with the participant wearing light clothing and without shoes within the participant’s household compound. Body weight will be taken to the nearest 0.1 kg using a SECA digital scale placed on flat ground. Height will be taken in a standing position with heels perpendicular to the portable stadiometer, measured to the nearest 0.1 cm. BMI will be calculated as body weight divided by height squared (kg/m^2^). Overweight will be defined as BMI ≥ 25 kg/m^2^ but < 30 kg/m^2^ and obesity is defined as BMI ≥ 30 kg/m^2^ [40]. Waist circumference will be measured and recorded to the nearest 0.1 cm using a non-stretchable measuring tape at the mid-point between the lower margin of the last rib in the mid-axillary line and the iliac crest according the WHO guidelines [41]. Abdominal obesity will be defined as waist circumference ≥ 102 cm.

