Similar methods of DID will be used for the analysis of secondary outcomes including changes in mean DBP, changes in the proportion of other CVD risk factors, and changes in 10-year risk for CVD event. The 10-year risk for CVD event will be estimated using the Globorisk office charts [46] specific for Tanzania. The Globorisk office chart is a simple instrument which requires age, SBP, self-reported smoking status, and gender to predict one’s 10-year risk for CVD event. For participants in the intervention, changes in 10-year risk will be assessed by comparing the risk at baseline and end-line assessment.

Missing data and loss to follow-up are major issues of concern as they may compromise inferences of any trial. Efforts will be made during trial implementation to ensure complete follow-up and minimize missing data and loss to follow-up. During analysis, we will assess the magnitude and compare the baseline characteristics of participants lost to follow-up and those with end-line assessment data to see if there is any specific pattern of missing and loss to follow-up. Since there is no single universal method for handling missing data in trials [47], it is difficult to decide a priori the best way to handle missing data for this study. The decision to exclude missing data from final analysis or use multiple imputation analysis will be made after examining the magnitude and pattern of missing data. For all analyses, a two-sided *p* value of ≤ 0.05 will considered statistically significant.

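### Body weight is assessed only as a change in the proportion overweight or obese, although BMI is measured continuously; mean BMI should be added as the tested weight outcome

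*Protocol article*

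**What the plan says.** Under Secondary outcomes, item (2) is "change from baseline in the proportion of overweight/obesity, smoking, alcohol intake, unhealthy dietary habits, and physical inactivity". This is the only outcome on body weight; no mean BMI or mean weight outcome appears anywhere in the article.

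Under Anthropometrics, "Body weight will be taken to the nearest 0.1 kg using a SECA digital scale placed on flat ground", height is recorded to 0.1 cm, and BMI is computed from the two. The categories are then given: "Overweight will be defined as BMI ≥ 25 kg/m^2^ but < 30 kg/m^2^ and obesity is defined as BMI ≥ 30 kg/m^2". They appear as definitions, and no reason is given for making a category the trial outcome.

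Under End-line survey, "Outcome variables of interest assessed during baseline will be re-assessed during end-line", in the participants of the intervention study. Under Quantitative data, difference-in-differences methods like those for systolic pressure are to be used for "changes in mean DBP, changes in the proportion of other CVD risk factors". Systolic and diastolic pressure are therefore compared as means, although the Blood pressure section gives cut-offs for them too (140 and 90 mmHg).

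**The concern.** An ideal or normal body weight is among the messages that the community health workers deliver, so the weight outcome tests part of the intervention. If overweight and obesity are taken together as BMI of 25 or more, a participant contributes only by crossing 25 between the two surveys. A fall from 34 to 30.5 counts the same as no change at all. With six villages per arm, an outcome that moves in so few people may show nothing even when mean BMI falls. The Discussion promises evidence on reduction of risk factors, and results are to go to the Ministry of Health, so a null on this item could be taken to mean that weight did not change.

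**Working it through.** **1. The plan's own figure.** The trial is "calculated to provide an 80% power to detect a ≥ 6.5 mmHg difference in mean SBP", with SD 15 mmHg, intracluster correlation (ICC) 0.03, 20% attrition and 258 participants in six villages per arm. Evaluable per village: 258 × 0.8 / 6 = 34.4. Design effect: 1 + 33.4 × 0.03 = 2.002. Standard error: 15 × √(2 × 2.002 / 206.4) = 2.089. Ratio: 6.5 / 2.089 = 3.11. A two-sided 5% t-test with 10 degrees of freedom (12 villages less 2) has power 0.800, so 258 per arm reproduces. No power is stated for the weight outcome.

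**2. Inputs for BMI.** The Background gives only population prevalences (obesity 23%; overweight 5.4% in the 1990s). Everything else is assumed: baseline mean 23.5–25 kg/m², SD 4–5, SD of 12-month change 1.5–2.0, village ICC of change 0.01–0.03 (0.03 is the plan's value for systolic pressure), effect 0.4–0.8 kg/m², and 34 analysed in each of six villages per arm.

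**3. One scenario by formula.** Take mean 25, SD 5, change SD 1.5, ICC 0.03, effect 0.6.
- *Everyone shifts by 0.6.* SE of the difference in mean change = 1.5 × √(2 × (0.03 + 0.97/34) / 6) = 0.210. Ratio 0.6 / 0.210 = 2.86; power 73% (10 df). By simulation, the proportion differs by an expected 4.7 points and has 25% power.
- *Only those at BMI ≥ 25 shift.* With mean 25 this is half the participants, so the mean effect over all is 0.3. Ratio 1.43; power about 25%.
- *Mean BMI within that subgroup.* About 17 per village: SE = 1.5 × √(2 × (0.03 + 0.97/17) / 6) = 0.256. Ratio 2.35; power about 56%.

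With mean 23.5, the share at BMI ≥ 25 is 1 − Φ(1.5/4) = 35% or 1 − Φ(1.5/5) = 38%, so the dilution is greater.

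**4. All scenarios.** Simulation with a t-test on village means (10 df), for change in BMI and for change in the indicator BMI ≥ 25. There are 16 settings per effect. Ranges take the widest ends over repeated runs, which differ by a point or two.

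| Effect (kg/m²) | All shift: mean BMI | All shift: proportion | Only BMI ≥ 25 shift: mean BMI, all participants | Only BMI ≥ 25 shift: proportion |
|---|---|---|---|---|
| 0.4 | 24–58% | 9–17% | 6–20% | 6–9% |
| 0.6 | 48–89% | 16–32% | 11–36% | 8–13% |
| 0.8 | 72–99% | 28–49% | 15–56% | 11–19% |

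When everyone shifts, mean BMI gains about 13 to 64 points of power. When only those at BMI ≥ 25 shift, the gain over all participants is about −2 to 39 points. In that case mean BMI change within the subgroup has 14–89% power, 7 to 71 points more than the proportion.

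**5. Information, with different inputs.** Prevalence of BMI ≥ 25 of 23–50%, SD 4–5, baseline to 12-month correlation 0.80–0.95, uniform effect 0.5–1.0. Between 78% and 92% of intervention participants score zero, and the change in the indicator keeps 9–31% of the information in BMI change. In the central case (35%, SD 4, correlation 0.9, effect 0.5), SD of change = 4 × √(2 × 0.1) = 1.79, 86.6% score zero and the proportion moves by 0.045. SD of the indicator change ≈ √(0.134 − 0.045²) = 0.363. Relative efficiency ≈ (0.045/0.363)² / (0.5/1.79)² = 0.0153/0.0780 ≈ 0.20 (0.19 unrounded).

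**The case against.** The strongest objection concerns who is expected to lose weight. Participants enter on blood pressure, not weight, and the message on ideal body weight does not ask lean people to get thinner. Power figures that let every participant's BMI fall count loss in lean participants as benefit. This stands: the responder-only columns show that mean BMI over all participants may then do little better than the proportion, and is itself mostly underpowered. It is why the subgroup analysis belongs in the fix.

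Second, prevalence is a legitimate public-health target. The protocol speaks throughout of proportions of the other risk factors, and being within the healthy range matches the message. This stands as a reason to keep the proportion, but not to leave the measured scale unused.

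Third, a reader might infer that a move from obese to overweight is bound to count as no change. The protocol joins the two terms in the outcome but defines them as separate categories, and never states a single indicator at 25. The combined reading is the natural one, but it is a reading.

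Fourth, this is one item in one of five secondary outcomes, no power is claimed for it, and an analysis plan that is not shown could add mean BMI. That limits the importance. The point remains because the outcome itself is fixed in the protocol as a proportion.

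**Conclusion.** The concern holds in limited form. The protocol fixes its only weight outcome as a change in a proportion while holding paired, continuous BMI, and so discards much of the information on weight change.

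A reader might conclude that most of the power is lost. The documents do not support that without conditions, because they contain none of the BMI inputs:
- The large gains need a shift across all participants. With a response confined to BMI ≥ 25, the gain over all participants can vanish, and the clear gain is in the subgroup.
- Where mean BMI has power near 1, less than half may be lost (1.00 against 0.57 in one scenario).
- If baseline were ignored, relative efficiency would be 0.52–0.64. The plan uses change from baseline, so the paired figures are the relevant ones.
- A larger village ICC narrows the gap. With mean 25, SD 5, change SD 2 and a uniform effect of 0.6, power is 38% against 18% at ICC 0.05, and 25% against 15% at 0.10.

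Nor would a null on the proportion necessarily be the work of the scale: at small effects, mean BMI would often be null too. All these powers treat the 12 villages as independent units, as reproducing the plan's 258 per arm also requires. The primary outcome is untouched.

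**What to change.** In secondary outcome (2):
- Add the difference between arms in mean BMI (kg/m²) at 12 months, adjusted for baseline BMI and fitted with the same village-level model as systolic and diastolic pressure, as the tested weight outcome.
- Pre-specify the same analysis in participants with baseline BMI of 25 or more. The baseline survey precedes village assignment, so membership of this subgroup cannot be affected by the arm.
- Keep the proportion overweight/obese as the reported public-health summary, and state whether it means BMI of 25 or more.

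The cost is a line or two of outcome wording and one or two models on data already to be collected, with no new measurements or participants. A mean difference is less directly readable as a prevalence, which the retained proportion covers. Trial status says that recruitment has not begun, so the change can be made before any outcome data exist.
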